## **FCP screening tool (Aim 1 new participants, Aims 2-3)**

1. Do you provide help or support to a family member or loved one who is/was enrolled in VNS Health hospice care? (Must have a loved one or family member enrolled in VNS Health hospice)
2. Does/Did your family member/[insert relationship] have memory problems or dementia? (Must have memory problems or dementia)
3. Are you over 18 years old? (Must be 18 years or older)
4. Do you identify as African American, black, white, or Caucasian? (Must identify as one of these categories. May identify as both or additional races/ethnicities.)
5. Does/Did your family member/[insert relationship] live in a nursing home or other long-term care facility [when they died]? (Must receive/have received home hospice care)
6. For how long [have you been caring/did you care] for your family member/[insert relationship]? (Must provide care for at least 1 month)
7. About how many hours a week [do/did] you spend caring for your family member/[insert relationship]? (Must provide at least 8 hours of care/week)
8. Please name as many animals as you can in one minute. (Write down every animal mentioned. Must name 15 different animals)

Note. Past tense language allows for inclusion of bereaved care partners in Aim 1. For Aims 2 and 3, all participants must be care partners of current hospice patients.

##### 6. Consent forms and additional PHI authorizations.

For all three Aims, and prior to participating in any study activities, all FCP, clinician, and research/content expert participants will provide informed consent. Informed consent will be obtained by study personnel in person, by telephone, or using an electronic consent process. The format of informed consent will be based on the study participant’s stated preference. Study participants will sign the approved informed consent or e-consent form and be provided with a copy of the signed document.

For Aim 3 we will also have an oral consent option and are requesting an alteration of written consent in order to provide oral consent as an alternative to written or e-consent, should this be the participant’s preferred method of providing consent. We are adding oral consent as an option due to feedback from previous aims. We found that one reason that hospice caregivers were not participating was that many of them are very busy. We hope that by offering an oral consent option, this will allow more caregivers to participate by reducing the burden of study participation and include individuals in the study who may not have access to technology to provide e-consent. Please see attached oral consent script, oral consent form, and changes in the protocol to reflect this addition. After obtaining oral consent over the phone, we will mail or email the consent form to the caregiver to have as a copy. We will still maintain written consent as an option for caregivers who want to meet in-person.

Informed consent will be conducted by study personnel trained in consent procedures. Study personnel will review the study, allowing the participant to ask questions at any time during the discussion. The main points addressed by study personnel include explaining that participation is voluntary, why the study is being done, study procedures, potential risks and benefits of participation, and how participant confidentiality will be protected. Electronic copies of informed consent documents will be stored on a secure server that only authorized study personnel are credentialed to access. E-consent forms will be collected, and oral consent will be tracked and stored in a secure, HIPAA compliant database such as REDCap, that only authorized study personnel are credentialed to access.

Copies of consent forms for Aims 1-3 and the oral consent procedures for Aim 3 are included in the application package. An example of the electronic informed consent form can be found here:

<https://redcap.rwjms.rutgers.edu/surveys/?s=XMDTAPVMxS>

A modification has been made as of May 2024 to increase the number of family caregivers with whom clinicians can be matched to offset caregiver attrition and maximize participation among clinicians that may have an opportunity to match with more than 4 family caregivers. Study staff will return to currently enrolled clinicians and ask if they are willing to match with more than 4 caregivers if such matches are available, collecting verbal consent in the process.

##### 7. Request for Waiver of Authorization

In addition to obtaining consent from FCP, clinician and research/content expert participants, we are requesting a waiver of consent and HIPAA authorization to access electronic hospice records for the following reasons.

**Planning**. We will extract information about the care partner burden field and the individuals for whom it is completed in the electronic hospice record, including care partner burden scores, dates recorded, patient gender, race, ethnicity, age, primary and comorbid diagnoses, dates of enrollment and discharge, discharge status, care partner relationship to patient, and clinician recording burden rating. We will also extract similar information for fields relevant to the content of the educational training videos (e.g. care partner education, prognostic understanding, etc.). Analyzing this information will allow us to tailor educational videos and training materials for clinicians. As this extraction will involve several thousand records, a majority for deceased individuals, it is not possible to obtain this information without a wavier of authorization.

**Aims 1-3.** We request the waiver to view electronic hospice records of home hospice patients in order to identify FCP who are potentially eligible to participate in all three aims of the study. It is not possible to identify potentially eligible FCP without the waiver of authorization.

**Aims 2-3.** We request the waiver to view electronic hospice records of home hospice patients of study-enrolled FCP to obtain the dates on which clinicians visit these patients. We require this information in order to know when to follow up with FCP to assess intervention fidelity and collect outcomes data (burden, self-efficacy, etc.) and when to follow up with clinicians to assess intervention fidelity. Because all patients have dementia, it is not possible to obtain information about hospice clinician visit timing from patients directly.

**Aim 3.** We request the waiver to extract outcome-related information from electronic health records of home hospice patients whose FCP are enrolled in the pilot RCT (Aim 3). We will extract his information 3 and 6 months following FCP participation in the pilot RCT and so anticipate that a majority of the hospice patients for whom the information is extracted will be deceased. For these individuals, we will extract information regarding their hospice enrollment and services, including: gender, race, ethnicity, age, dates of enrollment and discharge, discharge status, care partner burden and dates recorded, care partner relationship to patient, dates and duration of hospice interdisciplinary team visits, and the clinician who made the visit.

A Request for Waiver of Authorization Form is included in the application.

##### 8. Data to be employed

Please see Table 1 (above) and Appendix for data collection instruments at the end of the document. Data collection procedures will be conducted by trained research staff and done in-home, at VNS Health headquarters, at Rutgers University, by phone, by videoconference or online surveys as outlined in the protocol above. Data will be collected by research staff or online questionnaires and entered into and stored in a HIPAA compliant database such as REDCap.

##### 9. Analytic Methods.

**Feasibility/Acceptability.** We will assess feasibility and acceptability using accrual rates, attrition rates, adherence to the study protocols, use of the intervention (e.g. educational video views, training completion, use of assessment tool), and participant evaluations of perceived utility and acceptability of the intervention using a feasibility questionnaire (Appendix).

**Qualitative analysis.** We believe sample sizes will be sufficient to obtain thematic saturation in qualitative analyses. If needed, we will continue to collect data at all stages until achieving thematic saturation. Data coding and analysis will be informed by a responsive model in which blocks of information are combined based on the theme they represent. Trained raters will independently review the transcripts and identify passages that include suggestions for inclusion and/or modifications to the intervention. Raters will then organize these passages into categories reflecting single themes, discuss these themes, and revise themes until consensus is reached. Identified themes will inform modifications to the intervention. Additionally: **Aim 1**. A study team member will take notes during stakeholder interviews. Relevant notes and written feedback from stakeholders will be incorporated into training and tool refinement. **Aim 2**. Participant responses to questions about intervention components will be recorded in a secure database (e.g. REDCap). Responses will be systematically analyzed by research team members, under the supervision of the Principal Investigator, to identify items for revising and finalizing the training and tool and implementation processes. When participants provide responses by telephone or videoconference, we will record responses and transcribe them into REDCap and analyze them for themes.

**Quantitative Analysis.** We will calculate descriptive statistics to characterize the sample of participants in each aim. **Aim 3.** We will calculate changes in participant outcomes by comparing individual responses to questions at baseline and various points in time after exposure to the training and tool. To establish preliminary efficacy, we use a continuous measure of FCP burden using the 12-item Zarit Burden Interview (ZBI). The primary analysis will be a full information mixed model approach. We base primary power calculations on a more conservative two-group comparison of endpoint means (differences in means) with possible attrition. We assumed σ (variance)=9.8 (for the ZBI), α=0.05 R (reliability)=0.9 and g=2 groups (intervention and usual care). We estimated the variance inflation factor from the design effect of clustering within clinician: Vif=1+(Nc-1)Icc=1.09 (with cluster size, Nc=4 patients per provider) and intracluster correlation coefficient (Icc=0.03). Assumptions are based on earlier care partner studies in racial/ethnic minority samples. Assuming power of 0.80, with 80 per group, we would be able to detect a moderate effect size (Cohen’s d89=0.49), equivalent to ~4.80 points on the ZBI. We also examined sample size requirements for the detection of other endpoint differences: 4.0, 4.5, and 5 points on the ZBI. We examined different scenarios regarding correlations between baseline and follow-up outcome measures. We modified the formula from Fleiss (p 4-5) to include different scenarios related to correlations between the two waves of data: n*= [4(1-ρ)(σ2)(Zα/2+Zβ)2] / δ2 adjusting for unreliability: n=(n*Vif) / R.

The power calculation is based on a sample of 48 care partners and 4 care partners per clinician, and ρ (correlations between repeat measures of each person in waves of data)=0.5, 0.6 and 0.7, the resulting estimates of minimal detectable intervention arm differences are δ=6.21, 5.56, and 4.81 for ZBI, thus demonstrating that a medium effect size (Cohen’s d=0.49 to 0.63) could be detected with this sample size. As the study progresses, actual enrollment may change and analyses will be adjusted accordingly.

We believe FCP burden will be the primary outcome for this intervention. However, as this is a pilot trial, we want to ensure we identify the appropriate outcome for a fully-powered RCT, and so will also collect information about changes in FCP self-efficacy and preparedness and clinician knowledge and confidence in EOL dementia care. The purpose of the pilot testing is to determine feasibility of implementing the training and tool in a clinical setting and establish their preliminary efficacy in reducing FCP burden, collect normative data, and identify the appropriate outcome so that a fully-powered RCT can be conducted in future research (R01). In order to lay the groundwork for a future pragmatic trial of the intervention, we will also collect exploratory data existing in the hospice EHR including care partner burden, information related to educational videos content (e.g. care partner education, prognostic understanding, etc.), discharge status, and patterns of IDT visits to PLwD.

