## **Aim 3. Pilot RCT**

Sample. 24 clinicians from up to 14 hospice clinical teams and 96 Black and White FCP. Approximately 12 clinicians and 48 FCP will be randomized to the intervention. Approximately 12 clinicians and 48 FCP will be randomized to usual care. We may enroll up to 18 clinicians in each arm (36 total) to allow for attrition and some clinicians not matching with 4 caregivers to reach goal of 48 FCP in each arm.

*Inclusion Criteria.* Same for FCP and clinicians as Aim 2.

*Exclusion Criteria.* Same for FCP and clinicians as Aim 2. Additionally, clinicians and FCP are excluded if they participated in Aim 2.

We are requesting a waiver of authorization to access electronic hospice records for three purposes: 1) screening to identify potential FCP participants based on hospice patient criteria described above; 2) monitoring clinician visits during the intervention to coordinate post-clinician visit data collection; and 2) identify outcome-relevant information including discharge status, number and timing of clinician visits, and clinician assessment of FCP burden.

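### The primary power statement is for 80 care partners per group although about 48 per arm are planned, and neither set of power figures contains the attrition the text mentions

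*Protocol*

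**What the plan says.** Protocol section 9 (Analytic Methods, Quantitative Analysis) names a full-information mixed model as the primary analysis. It bases the primary power calculations on a "more conservative two-group comparison of endpoint means (differences in means) with possible attrition". The inputs are "σ (variance)=9.8 (for the ZBI), α=0.05 R (reliability)=0.9 and g=2 groups", with the design effect "Vif=1+(Nc-1)Icc=1.09 (with cluster size, Nc=4 patients per provider" and an intracluster correlation of 0.03. The result is "Assuming power of 0.80, with 80 per group, we would be able to detect a moderate effect size", "equivalent to ~4.80 points on the ZBI". The paragraph ends with a sample size formula that includes ρ, the correlation between the two waves: "n*= [4(1-ρ)(σ2)(Zα/2+Zβ)2] / δ2 adjusting for unreliability: n=(n*Vif) / R".

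The next paragraph is based on 48 care partners, 4 per clinician. For ρ = 0.5, 0.6 and 0.7 it gives detectable differences of 6.21, 5.56 and 4.81 points (d from 0.63 down to 0.49).

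The planned size elsewhere is 48 per arm. Section 4 (Aim 3. Pilot RCT) has "Approximately 12 clinicians and 48 FCP will be randomized to the intervention" and the same number for usual care. Section 2 (Aim 3) and section 3 (Aim 3: EDITH-HC pilot RCT) agree, and section 3 says that the estimated enrolment was being reduced.

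**The concern.** Two sample sizes stand side by side as the basis for power, and the one introduced as primary belongs to a larger trial than the one planned. The 80-per-group sentence is current text and is not labelled as superseded. The mismatch is easy to miss, because d = 0.49 and about 4.8 points appear in both paragraphs.

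The section also says that the primary calculations allow for attrition, so a reader may take the figures as already discounted for loss.

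A stated purpose of this pilot is preliminary efficacy on FCP burden, ahead of a fully powered trial. A reader who relies on the first statement would credit the simple endpoint comparison with 80% power for 4.8 points, which it does not have at 48 per arm.

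**Working it through.** **Inputs (Protocol section 9).** σ = 9.8, two-sided α = 0.05, power 0.80, R = 0.9, Vif = 1 + 3 × 0.03 = 1.09. The protocol labels σ a variance, but the printed results follow only if 9.8 is a standard deviation. Read as a variance, 48 per arm would give 1.97, 1.76 and 1.53 points. (Zα/2 + Zβ)² = (1.960 + 0.842)² = 7.849.

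**Formula.** Solved for the detectable difference: δ = √[4(1 − ρ) × σ² × 7.849 × Vif / (R × n)], with n per arm. At ρ = 0.5 the leading factor is 2, which is the ordinary two-group comparison of endpoint means.

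**Reproducing the 80-per-group figure.**
- 2 × 96.04 × 7.849 × 1.09 / 0.9 = 1,826
- δ = √(1,826 / 80) = 4.78 points, d = 0.49
- n for 4.80 points = 1,826 / 4.80² = 79.2 per arm (79.9 if the unadjusted n is first rounded up to 66)

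The statement reproduces as an endpoint comparison with all 80 analysed.

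**Same basis at 48 per arm.**
- δ = √(1,826 / 48) = 6.17 points, d = 0.63
- Standard error of the difference = √[2 × 96.04 × 1.09 / (0.9 × 48)] = 2.20
- Power for 4.80 points = Φ(4.80 / 2.20 − 1.96) = 0.59

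**Reproducing the 48 figures.**

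| ρ | Stated δ | Recomputed, n = 48 per arm | n implied by stated δ |
|---|---|---|---|
| 0.5 | 6.21 | 6.17 | 47.4 |
| 0.6 | 5.56 | 5.52 | 47.3 |
| 0.7 | 4.81 | 4.78 | 47.4 |

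So the 48 is per arm. As a total (24 per arm) it would give 8.72, 7.80 and 6.76.

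**Why d = 0.49 appears twice.** (1 − 0.5) / 80 = (1 − 0.7) / 48 = 0.00625. The move from ρ = 0.5 to ρ = 0.7 exactly offsets the 40% smaller sample.

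**Attrition.** The formula has no term for it. With 10% loss the 80-per-group figure would be 5.04, not 4.80, and the 48 figures would be 6.50, 5.81 and 5.04, not 6.21, 5.56 and 4.81. The protocol gives no rate, so the rates below are assumptions. Vif is held at 1.09.

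| Loss | Analysed per arm | δ, ρ = 0.5 | δ, ρ = 0.7 | Power at the stated δ |
|---|---|---|---|---|
| 0% | 48 | 6.17 | 4.78 | about 0.80 |
| 10% | 43.2 | 6.50 | 5.04 | 0.76 |
| 20% | 38.4 | 6.90 | 5.34 | 0.71 |
| 30% | 33.6 | 7.37 | 5.71 | 0.66 |

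If Vif shrinks with the clusters, the changes are small: at 30% loss, 7.25 instead of 7.37 and 5.62 instead of 5.71.

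**The case against.** The strongest reply is that the protocol already prints the right numbers. Its first figure for 48 is 6.21 at ρ = 0.5, which is the endpoint comparison, and 4.81 is openly tied to ρ = 0.7. A reader who finishes the section sees a range of 4.81 to 6.21. This stands, and it limits the point: the arithmetic is essentially sound, and the fault is a sentence that does not fit the design. It does not remove the fault, because the 80-per-group claim is neither withdrawn nor marked as superseded.

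Four stronger readings are tempting, and the protocol does not support them.
- *The 48-per-arm paragraph claims to allow for attrition.* It makes no such claim. The attrition phrase describes the primary power calculations and comes before the 80-per-group sentence. What can be said is that neither set of figures contains any loss.
- *The protocol quietly drops a conservative method.* There, conservative contrasts a simple two-group comparison with the planned mixed model. The formula with ρ is disclosed in the same paragraph as the 80-per-group figure.
- *The trial cannot detect 4.8 points on its own inputs.* It can at ρ = 0.7, which is one of those inputs. The 59% belongs to the endpoint comparison (ρ = 0.5) and is not the power of the mixed model.
- *Section 7 shows heavy loss of ZBI data.* There the investigators "anticipate that a majority of the hospice patients for whom the information is extracted will be deceased". That concerns record extraction 3 and 6 months after FCP participation and does not say how many FCP will lack a follow-up ZBI.

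Dividing by R = 0.9 has the same numerical effect as inflating for 10% loss, so one might say attrition is covered that way. The protocol names that factor as reliability, and one factor cannot serve for both.

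Section 6 allows clinicians more matches to offset caregiver attrition, and section 9 says enrolment may change. Neither gives a number, and the goal in section 4 stays at 48 per arm. A full-information model also uses partial follow-up, so treating each lost FCP as contributing nothing is pessimistic.

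Finally, this is a pilot, and no stated progression decision depends on the 80-per-group sentence.

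**Conclusion.** The point holds as an internal inconsistency in stated power. The primary statement is for 80 per group and the plan is 48 per arm. On the same endpoint basis the detectable difference rises from about 4.8 to about 6.2 points (d from 0.49 to 0.63), and power for 4.8 points falls from 80% to about 59%. This rests on the protocol's own α, R, Vif and σ, with 9.8 read as a standard deviation.

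The mention of attrition is also wrong as written, because no rate or term is included and both calculations reproduce with essentially no loss. The size of any attrition effect is unknown; the 10% to 30% range is illustrative. The 80 probably remains from the plan before enrolment was reduced, which is an inference and not something the protocol states.

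**What to change.** In Protocol section 9:

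1. Delete the 80-per-group sentence.
2. Label the remaining figures as 48 per arm. Lead with about 6.2 points (d = 0.63) as the endpoint comparison, equal to ρ = 0.5.
3. State 4.8 points (d = 0.49) only with its conditions: ρ = 0.7 and no attrition.
4. Either remove the phrase about possible attrition, or recompute on the number expected to give a follow-up ZBI over a stated, assumed range. For example, 10%, 20% and 30% loss give about 6.5, 6.9 and 7.4 points at ρ = 0.5, and 5.0, 5.3 and 5.7 at ρ = 0.7, with Vif at 1.09.

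This changes text only: design, enrolment goal and analysis stay as they are. The cost is that the stated detectable difference looks less favourable.

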##### 10. Statement of the risks/benefits for the study subjects.

This is a minimal risk study to develop, pilot test the feasibility, acceptability, and preliminary efficacy of an intervention consisting of educational videos and a care partner assessment tool.

**Aim 1.** Intervention Development. We do not anticipate that participants will benefit directly from providing feedback on the intervention materials. Risks to study participants are minimal and may include FCP becoming distressed when reviewing material about end-of-life care and potential stressors.

**Aim 2.** Single Arm Pilot. The purpose of this aim is to test feasibility and acceptability of implementing the intervention within a hospice clinical team and a small number of family care partners. We do not anticipate participants will benefit from their participation. Clinicians may improve their knowledge of dementia caregiving at end of life and their confidence in supporting patients living with dementia and their FCP. FCP may feel reduced burden and/or increased self-efficacy and preparedness after pilot testing the assessment tool. Risks to study participants are minimal and may include becoming distressed when identifying stress or issues related to their family caregiving. The intervention is designed to fall within the normal scope of nurses’ and social workers’ jobs, and so in most cases, they will be equipped to address FCP distress. Clinicians will follow normal VNS Health procedures should a FCP become distressed.

**Aim 3.** Pilot RCT. This aim pilot tests feasibility and acceptability of implementing the intervention on a larger scale. There are no anticipated benefits for control group participants. In the intervention group, clinicians may improve their knowledge of end-of-life dementia caregiving and confidence in supporting patients and their FCP. FCP may feel reduced burden and/or increased self-efficacy and preparedness after using the assessment tool. For both groups, FCP may feel burdened answering survey questions after clinician visits. We have kept c burden to a minimum to reduce this risk. There are no anticipated additional risks for control group participants. Intervention group FCP participants may feel distressed when identifying stress or issues related to their family caregiving. The intervention is designed to fall within the normal scope of nurses’ and social workers’ jobs, and so in most cases, they will be equipped to address FCP distress. Clinicians will follow normal VNS Health procedures should a FCP become distressed. Additional steps to minimize risk and address adverse events are outlined in the Data Safety Monitoring Plan included in this application.

**Aims 1-3.** All study subjects will be free to refuse to answer any questions or to discontinue study participation at any time. As always, there is the possibility that participant confidentiality will be breached. We will take steps to minimize this possibility and protect participant confidentiality as outlined in the following section.

**Aims 2-3**. FCP participants may become emotional or upset when completing the tool with clinicians because they are being asked to think about and address something that is causing them stress or worry. As VNS Health hospice clinicians routinely discuss and address with FCP sources of their stress, worry, and anxiety, they are well equipped to handle the types of emotions that may arise as part of completing the tool. In these situations, they will follow VNS Health standard procedures: nurses will offer a referral to the VNS Health social worker and/or spiritual care counselor. Social workers will use their training to help FCP cope with their emotions and offer referrals to the VNS Health spiritual care counselor and/or external resources as appropriate.

